## 4. Trial Objectives and Design

### 4.1. Trial Objectives

#### **Primary Objectives:**

To determine whether the addition of 120,000 IU monthly of vitamin D (cholecalciferol) supplement to standard treatments is more efficacious than placebo in improving outcomes (Positive and Negative Syndrome Scale Total score) at 6 month follow-up in those with First Episode Psychosis

#### **Secondary Objectives:**

To examine PANSS Total score and related sub-scores (Positive Scale, Negative Scale and General Psychopathology Scale) at 3 and 6 months, and a broader range of clinically-relevant outcomes; Global Assessment of Function (GAF), the Calgary Depression Scale, cardiovascular risk markers (Waist circumference, BMI, HbA1c, Total Cholesterol & CRP) and 25(OH)D concentrations at 6 months

We will examine primary and secondary outcomes in (a) all participants and (b) in a subgroup of the sample with suboptimal vitamin D concentrations at baseline (except for the secondary outcome of 25(OH)D concentrations which we will examine in all participants only).

#### **Tertiary Objectives:**

To collect data on inflammatory/immune markers

### 4.2 Trial Endpoints

#### **Primary endpoint:**

Total PANSS score at 6 month follow-up.

#### **Secondary endpoints:**

- Total PANSS score at 3 months
- PANSS Positive Scale subscore at 3 and 6 months
- PANSS Negative Scale subscore at 3 and 6 months
- PANSS General Psychopathology Scale subscore at 3 and 6 months
- Global Assessment of Function (GAF) at 6 months
- Calgary Depression Scale (CDS) at 6 months
- Waist circumference (cm) at 6 months
- BMI (kg/m^2) at 6 months
- HbA1c (mmol/mol) at 6 months
- Total Cholesterol (mmol/L) at 6 months

- CRP (mg/L) at 6 months
- 25(OH)D Concentrations at 6 months

**Tertiary endpoint:**

Descriptive and comparative analysis of inflammatory/immune markers

**4.3 Trial Design**

We propose a randomised, double-blind, placebo-controlled, parallel-group trial of Vitamin D supplementation compared to placebo in people presenting with their first episode of psychosis. Study participants will be on active study treatment for a maximum of 6 months – for specifics on time points please refer to sections 4.3 and 7.1.

#### 4.4 Trial Flowchart

[figure not shown]

## 5. Trial Medication

### 5.1 Investigational Medicinal Product

The basis for the Investigational Medicinal Products is Vigantol® oil (by Merck GmbH). Vigantol® is an oral liquid where 1mL solution contains 0.5 mg Cholecalciferol, equivalent to 20,000 IU vitamin D3.

In the DFEND trial, eligible patients will be randomised to receive either vitamin D3 120,000IU or placebo once monthly for 6 months in a 1:1 ratio.

The comparator drug of Vigantol® oil will be achieved by using an organoleptically matched triglyceride oil (Miglyol® 812 oil) for the placebo. Both active and placebo will be primarily packaged in identical glass bottles (fill volume 8mL). All medication will be labelled according to Annex 13 guidelines.

Active and placebo treatment will be administered orally as 6mL given in a graduated oral syringe by a trained researcher.

**Guy's & St Thomas' Pharmacy Manufacturing unit** is responsible for arranging the IMPs' manufacture, randomised labelling, packaging and final QP release for clinical trial use. Please refer to Summary of Product Characteristics for Vigantol® Oil and the Investigational Medicinal Product Dossier (IMPD) for more details about the active and placebo IMPs.

### 5.2 Dosing Regimen

The active treatment - Cholecalciferol (vitamin D3), 120,000 IU per month (equivalent to 4,000 IU per day), will be given orally as Vigantol® oil (by Merck GmbH) cholecalciferol dispersed in triglyceride oil as vehicle; containing 20,000 IU cholecalciferol per 1ml drop, and administered as 6mL given in a graduated oral syringe by a fully trained member of the research team. The placebo will be administered by the same trained research team and with the same method. Both will be administered monthly for 6 months.

### 5.3 IMP Risks

The Summary of Product Characteristics (SmPC) will be the Reference Document.

**Contra-indications** - Vigantol Oil must not be used in:

- Hypersensitivity to the active substance cholecalciferol or to any of the excipients
- Hypercalcaemia and/or hypercalciuria
- Hypervitaminosis D
- Renal osteodystrophy with hyperphosphatemia

**Special warnings and special precautions for use**

- During long-term treatment with a daily dose exceeding 1000 IU vitamin D the serum calcium values must be monitored.

- Special attention should be paid to patients treated with thiazide diuretics, to patients with nephrolithiasis history, to those suffering from sarcoidosis and during pregnancy. Special attention is also requested in patients with atherosclerosis, cardiac disorders, renal disorders and hyperphosphatemia. It is recommended to monitor levels of calcium, phosphates, magnesium, cholesterol (increases with higher doses) and alkaline phosphatase in serum

**Particular caution is recommended:**

- When taking additional doses of vitamin D, e.g. via other medicinal products
- In pseudohypoparathyroidism particular attention must be paid to signs of intoxication. There may be phases of normal sensitivity to vitamin D so that the dose has to be adjusted accordingly
- In pseudohypoparathyroidism after thyroid surgery Vigantol must be stopped as soon as recovery of the parathyroid glands is observed, in order to avoid vitamin D intoxication

**Interaction with other medicinal products and other forms of interaction**

- Digitalis (cardiac glycosides): Oral administration of vitamin D3 may increase the efficacy and toxicity of digitalis. Regular medical supervision is required including assessment of ECG, serum calcium, and possibly also digoxin plasma levels.
- Thiazide diuretics (e.g. benzothiadizine): The urinary calcium excretion may be reduced and the risk of hypercalcaemia may be increased.
- Barbiturates (e.g. phenobarbital) or phenytoin: plasma concentrations of 25-OH D may be decreased and metabolism to inactive metabolites may be increased,
- Corticosteroids: may decrease the efficiency of vitaminD3
- Vitamin D3 metabolites or analogues: It is recommended to combine with Vigantol only in exceptional cases and with monitoring of serum calcium levels.
- Rifampicin and isoniazid: may increase the metabolism of vitamin D3 and reduce its effectiveness.
- Large doses of vitamin D may cause hypercalcemia, increase cholesterolemia, lower alkaline phosphatase activity, tend to cause alkalosis
- Administration of medicaments containing magnesium aluminium (some antacids) is not recommended.

**Fertility, pregnancy and lactation**

During pregnancy and lactation sufficient intake of vitamin D is required. No data on acute or chronic toxicity of vitamin D levels on pregnant women are available. Hypercalcaemia caused by vitamin D overdosing during pregnancy may be associated with increased susceptibility to the effects of vitamin D, suppression of parathyroideal function, mental retardation, and aortic stenosis in child. On the other hand, significant hypovitaminosis D and osteomalacia in women may cause fetal or neonatal rachitis, hypoplasia of enamel and hypocalcemia. No teratogenic effects have been proven on laboratory animals after the doses 6-12 times higher than human doses have been administered. However, there are many cases when patients with hyperparathyroidism used 100,000 IU of cholecalciferol a day and delivered a healthy child have

also been recorded. Therefore, administration of larger doses of vitamin D3 on pregnant women should be considered by a specialist.

Pregnant women or those planning pregnancy will not be eligible to participate in the trial. We will not make it mandatory that women of child-bearing age are on contraception however we will monitor pregnancy status throughout the trial by reviewing pregnancy status with all female participants and administering a routine urine dipstick pregnancy test. We acknowledge that overdose of vitamin D must be avoided during pregnancy, because prolonged hypercalcaemia can lead to physical and mental retardation, supraaortic stenosis and retinopathy of the child. To address this safety issue, we have specifically chosen an amount of Vitamin D considered to be safe for use in pregnant women (Vigantol® 120,000 IU/month equivalent to 4000 IU/Day). We will continue to screen for pregnancy before giving each monthly dose. If we detect pregnancy in any female participants during the course of the trial, they will be withdrawn from the treatment. However, pregnancy tests will not be done for female participants who are permanently sterile or who are post-menopausal (no menses for 12 months without an alternative medical cause).

We will also ensure that all patients are made aware of the symptoms of hypercalcaemia (loss of appetite, nausea and vomiting, constipation and abdominal pain, increased thirst and frequent urination, fatigue, weakness, and muscle pain). If any of these symptoms are detected in between dosing visits, patients will be advised to contact their GP, so that their GP can arrange for a blood test for hypercalcaemia (and report hypercalcaemia as a suspected adverse reaction to the Trial Coordinating centre). First line treatment for hypercalcaemia is simple rehydration but if this is not effective then pharmacological interventions can be used. The GP will advise of this. The research team who administer the monthly IMP/placebo dose will also ask the patient if they have experienced any of these symptoms since they were last seen by the research team, this will be done routinely every month before any IMP/placebo administration. Should these symptoms be reported at a scheduled visit, a blood test will be offered to the patient to check calcium levels and ensure patient-safety.

Participants will be asked to refrain from taking vitamin D supplements (including multivitamins containing vitamin D); however, supplementation of up to 400IU/day will be permitted throughout the trial, as recommended by Public Health England.

#### 5.4 Drug Accountability

Vigantol® Oil is a vitamin based supplement and its main component cholecalciferol is a natural compound that is synthesized by the skin after exposure to UVB sunlight. We are raising the levels of a compound to which participants are naturally exposed in their everyday lives. This trial is classified as a Type B Trial for regulatory purposes.

Full IMP accountability will be maintained throughout the trial. IMP administration will be logged and then each bottle will be safely disposed of immediately after use. Used bottles will

not be returned to Pharmacy but will be disposed of in a sharps bin. Unused bottles will be returned to pharmacy and safely destroyed.

### 5.5 Storage of IMP

IMP/Placebo will be stored in Pharmacy according to manufacturer's guidelines.

### 5.6 Subject Compliance

Participants will be given IMP/Placebo orally by one of the research team with appropriate training and delegation to do so. The researcher will complete a source data worksheet to state the time, date, amount of IMP administered and the administering researcher for each dose administered throughout the study period.

As previously mentioned, the participants will be given the IMP/placebo once a month for 6 months. A dosing visit will be scheduled each month for a total of 6 months, where the initial dosing date, acts as the anchor date for all future visits (i.e. the first appointment should be scheduled a month after from the initial dose, and so on). A minimum of a 24-day interval between doses must be adhered to throughout the study to ensure that patients are not dosed too closely. A visit window of -2/+2 weeks from the anchor date will be set to allow room for missed/rescheduled appointments. If a dose is missed, the participant will be allowed to carry on with the trial and the next dose of treatment (either IMP/placebo) will be administered at the next scheduled time point; in such instances a protocol deviation will be logged.

We will seek permission from participants to voluntarily provide contact details of a close relative or friend plus at least 2 means of contact including email address, mobile phone number, landline phone number, in order to improve the likelihood of contacting patients at future follow-up points. We will note which is their preferred method. This information will be stored on a separate contact details form and will be kept in a locked file by the team administrator. We will make it explicitly clear that the contact details of a significant other will only be used in situations whereby we are unable to contact the participant in the first instance.

In the event that a participant decides they no longer wish to take the treatment (IMP/placebo) they will be encouraged to continue with the study, if agreeable they will be followed up at the main assessment points (6 months) but routine safety checks will not be offered, except for any due after their last dose of IMP and no drug will be administered. Participants are free to drop out from the study at any time.

For the follow-up assessment at 6 months a target visit window of -4/+6 weeks will be set to ensure follow-up data is collected. If the data can only be collected outside of this target visit window, it should be done anyway. For routine safety blood visits a -2 week window will be adhered to but an upper time frame will not be specified for collecting the safety bloods as these must be performed. Data collection will end at end of study defined in section 6.6.

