## 8.2 Procedures for Assessing Efficacy Parameters

Concerning efficacy, psychopathology will be assessed with the PANSS total score and related sub-scores, Global Assessment of Function (GAF) and Calgary Depression Scale, and 25OHD blood concentration levels at 6 month assessment visits.

Blood will be taken for 25OHD concentration at baseline and 6 months but this assay will not be performed until the trial is complete.

Concerning follow-up, all participants will be seen by trained research staff each month for the administration of the intervention. Research staff will assess outcomes at baseline, 3 (PANSS only) and 6 months, including anthropometric/cardiovascular assessments. With prior consent from the participant clinically relevant measures will be shared with the clinical teams to minimise duplication of assessments.

Primary outcomes will be assessed at 6 months in order to reduce the influence of attrition. Based on past research undertaken in London, we expect that up to 20% of FEP will drop out by 6 months.

Concerning safety, at study entry, all patients will be assessed with a physical examination, including weight, blood pressure, and pulse rate. Bloods will be taken at baseline and 3 months, in order to assess serum calcium (corrected for serum albumin) and parathyroid hormone (PTH) where indicated and at additional times if there is evidence of symptoms of hypercalcaemia. Side effects will be systematically assessed at each month prior to administration of the intervention (IMP/placebo).

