#### Power Calculation

Based on recently collected PANSS Total score in FEP patients collected as part of the Physical Health and Substance Use Measures in first episode Psychosis (PUMP) study ( $n = 190$ ), the mean (and standard deviation) score was 58.1 (15.0) units. Based on the number of new cases presenting to FEP services, and based on the annual counts of FEP patients recruited into similar studies, we predict that we will recruit and randomise 120 patients per year (i.e. 240 over two years).

The primary intention to treat (ITT) analyses will compare two equally sized treatment arms, treatment or placebo on the PANSS scale at 6 months post-randomisation. For the power analyses, we modelled two plausible scenarios. For the primary outcome (6 month follow-up), we assumed a 20% attrition proportion. After 20% attrition the effective sample size is 192 (96 in each trial arm).

Based on  $\alpha = 0.05$  and power = 80%, samples between 200 and 180 participants will be able to confidently detect mean PANSS total score group differences of between 6 and 6.3 units. This equates to a standardised effect of size of approximately 0.4 to 0.42.

Considering 90% power with the same power assumptions, we will be able to detect mean PANSS total score group differences of between 6.9 and 7.3 units (standard effect size from 0.46 to 0.49). Thus, we should be able to detect moderate effect sizes if present.

As a secondary objective, we also wish to estimate the average treatment effect in those participants who meet the vitamin D deficiency threshold. We assume 60% of the FEP

population have vitamin D concentrations below 50 nmol/L. At 6 months after 20% attrition (sample now = 192) and 60% who meet the vitamin D threshold, this will result in a projected sample size of 115.

Based on  $\alpha = 0.05$  and power = 80%, samples between 120 and 100 participants will be able to confidently detect mean PANSS total score group differences of between 7.7 and 8.5 units. This equates to a standard effect of size of 0.52-0.57. Considering 90% power with the same power assumptions, we will be able to detect mean PANSS total score group differences of between 9.8 and 8.95 units (standardised effect size from 0.60 to 0.65).

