## 10.2 Analysis

The primary analyses of efficacy will be based on the intention-to-treat sample, utilising all available follow-up data from all randomised participants. The significance level will be 5% (2-sided) for all specified main and secondary analyses with estimates and confidence intervals presented for all effects.

All descriptive analyses, recruitment rate, consent rate, loss to follow-up, departures from randomised treatment and the prevalence of serious adverse events post-randomisation will be reported and summarised by treatment arm over the course of the study. All causes of withdrawal from randomised treatment will be reported. BMI will be calculated using the following formula:  $\text{weight (kg)}/\text{height (m)}^2$ .

The main objective of the formal statistical analyses is to assess the effect of vitamin D supplementation on the primary outcome PANSS total Score at the 6 month follow-up time point. To this end linear mixed modelling (LMM) will be employed.

In such models the outcome variable measured at the post treatment time points (here 3 and 6 months) features as the dependent variable with, treatment arm (vitamin D or placebo), time (3 or 6 months), baseline PANSS and randomisation stratifier (ethnicity) included as covariates. The model will also contain a subject-varying random intercept to account for any correlation between the repeated measures.

Treatment effects on secondary outcomes will be assessed using similar modelling techniques, employing generalisations to non-normal data where necessary.

We will also estimate subpopulation (baseline vitamin D insufficient and sufficient) specific treatment effects for the primary outcome and secondary outcomes except for 25OHD blood concentration levels by including relevant interaction terms between baseline vitamin D insufficiency status and treatment group in the statistical models.

We expect there to be some missing data in the post-treatment outcomes variables. The LMM analyses are based on maximum likelihood and will provide valid inferences under a missing at random (MAR) missingness mechanism. We will explore predictors of missingness, if deemed suitable for adjustment we will include these as explanatory variables in the analyses. If post

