### Power calculation

Based on recently collected PANSS Total score in FEP patients collected as part of the Physical Health and Substance Use Measures in first episode Psychosis (PUMP) study (n = 190), the mean (and standard deviation) score was 58.1 (15.0) units. Based on the number of new cases presenting to FEP services and based on the annual counts of FEP patients recruited into similar studies, we predict that we will recruit 120 patients per year (i.e. 240 over two years).

The primary intention to treat (ITT) analyses will compare two equally sized treatment arms, treatment or placebo on the PANSS scale at 6 months post-randomisation. For the power analyses, we modelled two plausible scenarios. For the primary outcome (six-month follow-up), we assumed a 20% attrition proportion. After 20% attrition the sample size is 192, 96 in each trial arm).

Based on alpha = 0.05 and power = 80%, samples between 200 and 180 participants will be able to confidently detect mean PANSS total score group differences of between 6 and 6.3 units. This equates to a standardised effect of size of approximately 0.4 to 0.42. Considering

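### Protocol 5.6 does not assure a month-3 PANSS for participants who stop study drug, so month-3 missingness can depend on stopping treatment

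*Combined protocol and SAP*

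**What the plan says.** **After stopping drug.** Protocol 5.6 covers participants who no longer want the treatment: "if agreeable they will be followed up at the main assessment points (6 months) but routine safety checks will not be offered". The sentence goes on to keep any safety check due after the last dose. Protocol 6.5, on stopping drug only, says more broadly that the team will try to keep collecting follow-up data. Protocol 5.7 (supplement use) and 9.1 (pregnancy) encourage participants taken off drug to stay in the study, without naming visits.

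**Where the month-3 PANSS sits.** Protocol 8.2 says: "Research staff will assess outcomes at baseline, 3 (PANSS only) and 6 months". SAP 1.5 likewise adds a 3-month PANSS, with no condition on drug status. Table 1 and SAP section B place that rating in the safety-check column, Protocol 6.3 calls the visit a safety check, and Protocol 7.1 lists only baseline and 6 months as assessment visits.

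**Timing.** For routine safety bloods Protocol 5.6 sets a limit of two weeks early, and "an upper time frame will not be specified for collecting the safety bloods as these must be performed". SAP 1.6 repeats this. Neither document gives a window for the month-3 PANSS. The 6-month window opens four weeks early.

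**Use in the analysis.** Protocol 4.2 lists four month-3 secondary endpoints: PANSS total and three subscales. The efficacy analysis is by intention to treat, "utilising all available follow-up data from all randomised participants". The SAP 3.1.1 mixed model takes months 3 and 6 as outcomes, with a time-by-treatment interaction.

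**The concern.** The one rule that says what happens after a participant stops drug names a single time point, and it withdraws the type of visit to which the month-3 PANSS is attached. A site following 5.6 could reasonably skip the rating; a site following 8.2 could reasonably do it. Whether a month-3 score exists may then depend on whether the participant stayed on treatment.

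The likelihood-based model is valid when missingness is explained by what is in it: arm, baseline PANSS, ethnicity and the other observed PANSS score. Stopping treatment is not in it. If stoppers differ at month 3 beyond what those variables predict, and stopping differs by arm, the month-3 contrasts shift. They also lose precision. A participant who stops early and then misses month 6 has no PANSS after baseline at all.

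A smaller gap concerns timing. Without an upper limit, a late month-3 rating could fall inside the 6-month window, while the model codes time only as 3 or 6.

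**Working it through.** **1. The plan's own figure.** Inputs: "The significance level will be 5% (2-sided) for all specified main and secondary analyses" (Protocol 10.2); "Based on alpha = 0.05 and power = 80" per cent (SAP 1.8); "the mean (and standard deviation) score was 58.1 (15.0) units" (Protocol 10.1). Stated result: "samples between 200 and 180 participants will be able to confidently detect mean PANSS total score group differences of between 6 and 6.3 units". With n per arm and 1:1 allocation, detectable difference = SD × √(2/n) × (1.960 + 0.842).

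- N = 200: 15 × √(2/100) × 2.802 = 5.94 (5.97 using the t distribution)
- N = 180: 15 × √(2/90) × 2.802 = 6.26 (6.30)
- N = 240 × 0.8 = 192: 15 × √(2/96) × 2.802 = 6.07 (6.10)

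The plan's figures reproduce. They concern month 6 only, so no stated number changes.

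**2. Month-3 precision on the simple ratio.** The documents give no rate of stopping before month 3, so the rates here are assumptions. Suppose 10% are missing at month 3 for other reasons, leaving 240 × 0.90 = 216. Suppose a further 5%, 10% or 15% of the 240 stop drug, stay in the study and are not rated. The standard error (SE) varies as 1/√N.

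| Stop before month 3 | Month-3 N | SE ratio |
|---|---|---|
| 5% (12) | 204 | √(216/204) = 1.03 |
| 10% (24) | 192 | √(216/192) = 1.06 |
| 15% (36) | 180 | √(216/180) = 1.10 |

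As a cross-check, start from the plan's 192 instead. Losing 5%, 10% or 15% leaves 182, 173 or 163, and the simple detectable difference at 80% power goes from 6.07 to 6.22, 6.39 or 6.58 points. The last is a ratio of 6.58/6.07 = 1.08.

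**3. What the mixed model recovers.** This is a large-sample calculation for the SAP model (random intercept, treatment-by-time interaction, SD 15). Per arm, 96 are seen at month 6, 12 are seen at month 3 but lost before month 6, and a share of the 96 has no month-3 rating. The within-person correlation is assumed.

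| Correlation | Month-3 SE, 0% unseen | Month-3 SE, 20% unseen | Month-6 SE, both cases |
|---|---|---|---|
| 0.4 | 2.04 | 2.22 | 2.15 |
| 0.6 | 2.04 | 2.18 | 2.12 |
| 0.8 | 2.04 | 2.12 | 2.09 |

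At correlation 0.6 the month-3 increase is 2.18/2.04 = 1.07. The same loss (0.20 × 192 = 38 participants) gives √(216/178) = 1.10 on the simple ratio, so step 2 errs on the high side when stoppers return at month 6. The month-6 SE does not move.

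**4. Possible bias.** Same model. Assume stoppers score 5 to 10 points above their arm's mean at both occasions and are seen at month 6 only.

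- Stopping 10% in each arm: zero at both occasions.
- Stopping 15% on vitamin D and 5% on placebo: −0.11 to −0.65 points at month 3 and +0.02 to +0.11 at month 6, over correlations 0.8 to 0.4.

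A negative value favours vitamin D. The signs reverse if the imbalance reverses.

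**5. Early stoppers who also miss month 6.** Assume correlations of 0.5 (baseline with month 6), 0.6 (baseline with month 3) and 0.65 (month 3 with month 6).

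- Unexplained variance of the missing month-6 score given baseline only: 1 − 0.5² = 0.75.
- Given baseline and month 3: R² = (0.25 + 0.4225 − 2 × 0.5 × 0.65 × 0.6)/(1 − 0.36) = 0.2825/0.64 = 0.44, leaving 0.56.

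A month-3 rating would therefore carry useful information about the missing primary score, but only in this group.

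**The case against.** The strongest reply is that nothing forbids the rating. The exception in 5.6 can be read to cover a month-3 check for someone who stopped at month 1 or 2. Protocol 8.2 and SAP 1.5 schedule PANSS at 3 months for everyone, and 6.5 points the same way. This stands in part: it makes the texts conflicting rather than the rule absolute. It does not settle the matter, because the exception speaks only of safety checks, 6.5 names no visit, and 5.6 is the specific rule.

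Three stronger readings are tempting, and the documents do not support them.

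- **That month-3 data are not intention-to-treat.** Participants are analysed as randomised with whatever data exist. An unrated visit is missing data, not a change of analysis population.
- **That a rating at month 5 will be entered as month 3.** The open upper limit is worded for safety bloods; extending it to PANSS is an inference. For those on drug, the month-3 visit is also a dosing visit, and dosing visits carry a two-week window either side. SAP 3.1.3 summarises timing deviations by arm. What remains is that the PANSS has no window of its own and the handling of late ratings is unstated.
- **That the primary result is undermined.** Month-6 PANSS is still sought after drug is stopped, even outside its window, and steps 3 and 4 show little effect under the SAP model. The SAP also allows adjustment for baseline predictors of missingness, multiple imputation and sensitivity analyses for departures from missing at random. The imputation is only to be considered, however, and the sensitivity analysis is not specified.

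**Conclusion.** The point holds as a conflict between sections that leaves the month-3 PANSS unassured for participants who choose to stop drug. It bears mainly on the four month-3 secondary endpoints. Their SE would be about 3% to 10% higher for 5% to 15% stopping on the simple ratio, and less than that if stoppers return at month 6. Bias stays under one point in the scenarios tried and is zero when stopping is equal across arms. Stopping rates, correlations and score shifts are all assumptions.

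The month-6 primary estimate is largely protected, apart from lost information on early stoppers who also miss month 6. That protection rests on the SAP 3.1.1 model. The covariate list in Protocol 10.2 omits the treatment-by-time interaction; read literally, it would estimate one effect across both occasions and carry the month-3 gap into the primary result. The timing gap is secondary. Overall this is a worthwhile, cheap improvement rather than a flaw that invalidates the trial.

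**What to change.** - **Protocol 5.6:** state that PANSS is sought at both 3 and 6 months from every randomised participant who agrees, whatever their drug status. Reconcile 6.5, 7.1 and 8.2 with this.
- **Protocol 5.6 and SAP 1.6:** give the month-3 PANSS its own window, closing before the 6-month window opens. Leave the safety-blood rule untouched.
- **SAP, before unblinding:** state how ratings after that limit are handled, for example modelled by actual time or examined in a sensitivity analysis, rather than dropped.

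The cost is one existing rating by existing staff in a small number of participants: 12 to 36 on the 5% to 15% assumption, fewer if some are already rated. The visit change helps only participants whose month 3 is still ahead; the SAP statement applies to all.
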